| Subject Participation Duration: | 
Enrollment and initial assessment: 1 online assessment of 30 min
 
Intervention: 6 to 12 online sessions of 60 min in 6 to 12 consecutive weeks. A link to assessments will be sent before each session.
 
Post treatment assessment: 1 online assessment of 30 min to be completed within 14 days after completion of the intervention.
 
1-, 3-, and 6-month follow-up assessment: 3 online assessments of 30 min scheduled at 1-, 3-, and 6-months after completion of the intervention.
                                                                                                                                                                                                                                                                                                                                                                                                                                                                                                                                                                                                                                                                                                                                 |

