## 4.2 Study Outcome Measures

### 4.2.1 Primary Outcome Measures

Since the intervention is transdiagnostic and addresses several CMD, there will be three primary outcome measures. Changes in anxiety will be measured using the GAD7 scale. This is a 7-item instrument that measures generalized anxiety. Changes in depression will be assessed using the PHQ9 questionnaire, which is a 9-item instrument that measures depression. Both instruments have been chosen because they are short, easy to administer and have been widely used in research. Spanish versions of GAD7 and PHQ9 have been validated and used in Venezuelan and Peruvian populations. Furthermore, prior studies with this same population conducted by the main researcher have used these instruments. Regarding PTSD, changes will be measured using the PCL5 checklist which has been validated for its use in Spanish-speaking populations and utilized in research projects with similar populations. The LEC5, which identifies potentially traumatic events in the life course of the participants, will be used at baseline and in the follow-up assessments along with the PCL5.

The primary outcomes will be measured at baseline during screening and at endline 12 weeks after baseline in the case of waitlist control. In the intervention group, they will be assessed at baseline during screening, weekly (PCL5) or every two weeks (PHQ9 and GAD7) throughout the intervention before the next session, after the last session of the intervention and at 1-, 3-, and 6-month follow-ups after completion of the intervention. Participants will be sent a secure REDCap link, where they will be asked to answer each item of the instruments.

See appendix with the English and Spanish versions of the instruments.

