## 8 Study Intervention

The intervention in the present study was developed based on CBT techniques that have proven effective in the treatment of CMD. The intervention underwent a process of cultural adaptation following the Ecological Validity Model developed by Bernal et al. (1995), which has been used in numerous adaptations of psychosocial interventions, for instance by Perera et al. (2020 and 2022) in the adaptation of Problem Management Plus for its implementation with Venezuelan migrants in Colombia. In the following paragraphs we describe the intervention that resulted from this process. Figure 1 synthesizes its components:

[figure not shown]

Figure 1. Intervention components and implementation strategies.

In terms of the implementation, the intervention will be free of cost for the participant. It will comprise between 6 and 12 weekly sessions in consecutive weeks and will be delivered remotely via a video call. The sessions will last 60 minutes and before each session participants will be sent a link to REDCap to fill out the questionnaires for the measurement of the primary outcomes. After the session they will answer questions on the session’s acceptability. Since it has been identified that Venezuelan migrants have long working days and might also work in the weekends, we will offer many possibilities to schedule the sessions (e.g. Sundays, early in the morning, late at night...). There will be some flexibility will sessions cancellations and re-scheduling. However, at the beginning of the intervention some rules in this regard will be

Adaptation and assessment of a common element treatment protocol designed to improve mental health in forcibly displaced populations  
 Version 1, September 17, 2024  
 agreed upon between provider and participant. A general rule will be set in place and participants will be told that if they can re-schedule a maximum of three sessions in a row and of six sessions overall throughout the intervention. Otherwise, they will be excluded from the study

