|-------------------------------------|--------------------------------------------------------------------------------------------------------------------------------------------------------------------------------------------|-------------------------------------------------------------------------------------------------------------------------------------------------------------------------------------------------------------------|
|                                     | May-August 2025

Third group of 30 participants:
August -November 2025                                                                                                            |                                                                                                                                                                                                                   |
| Sessions 7 to 12                    | First group of 30 participants:
May - August 2025

Second group of 30 participants:
August-November 2025

Third group of 30 participants:
November 2025-February 2026 | Individually with provider
Remotely via Meet or WhatsApp videocall
60 min duration
Focus on other aspects relevant to mental health (emotional regulation, problem solving, adaptation related distress) |
| Assessments throughout intervention | January 2025 to February 2026                                                                                                                                                              | Remotely via REDCap secure link (PCL5 every week before the session, PHQ9 and GAD7 every 2 weeks before the session, acceptability and adherence every week after each session)                                   |
| Endline                             | May 2025 to February 2026                                                                                                                                                                  | Remotely via REDCap secure link (PHQ9, GAD7, LEC5 and PCL5)
12 weeks after first session in intervention group (or within 14 days of completion).
12 weeks after baseline in waitlist control group.        |

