| Assessment at 1-month follow-up     | August 2025 to January 2026                                                                                                                                                                | Remotely via REDCap secure link (PHQ9, GAD7, LEC5, PCL5) one month after endline (or a maximum of a month later).                                                                                                 |
| Assessment at 3-month follow-up     | October 2025 to March 2026                                                                                                                                                                 | Remotely via REDCap secure link (PHQ9, GAD7, LEC5, PCL5) three months after endline (or a maximum of a month later).                                                                                              |
| Assessment at 6-month follow-up     | January to June 2026                                                                                                                                                                       | Remotely via REDCap secure link (PHQ9, GAD7, LEC5, PCL5) 6 months after endline (or a maximum of a month later).                                                                                                  |
| Data Analysis                       | June 2026 to July 2027                                                                                                                                                                     | Data analysis will take place using data analytic software and be used for publication and dissemination in scholarly journals and conferences.                                                                   |

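### Endline runs from the first session or completion in the intervention arm but from baseline in the waitlist, so the arms are compared at unequal elapsed times

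*Protocol*

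**What the plan says.** Section 12 gives the two arms different clocks. In the intervention arm, endline is "12 weeks after first session in intervention group (or within 14 days of completion"; in the waitlist it is "12 weeks after baseline in waitlist control group". Section 4.2.1 places baseline at screening: "The primary outcomes will be measured at baseline during screening and at endline 12 weeks after baseline in the case of waitlist control". In the Section 12 table, screening comes before participation consent, randomisation and the first session.

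Elsewhere the intervention-arm assessment has no 12-week anchor. Section 2 describes it as "1 online assessment of 30 min to be completed within 14 days after completion of the intervention", and Sections 4.2.1 and 5 place it after the last session. Course length varies. Section 2 gives "6 to 12 online sessions of 60 min in 6 to 12 consecutive weeks", and Sections 8 and 9.1.2 allow up to six sessions to be rescheduled. Sections 5 and 8 link a higher number of sessions to a more complex presentation.

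The 1-, 3- and 6-month follow-ups are counted from completion in Sections 2 and 4.2.1, but from endline in Section 12. The Section 12 calendar puts endline at "May 2025 to February 2026" and the 6-month follow-up at "January to June 2026".

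**The concern.** Efficacy is the primary objective (Section 4.1), and the hypothesis in Section 15.1 is a comparison with the waitlist. Waitlist participants have one untreated measurement after baseline, their endline, and are then treated. That makes it the only controlled contrast in the trial. If one arm is measured at a fixed 12 weeks and the other at a time set by course length, the difference between arms mixes the treatment effect with whatever symptoms do by themselves over unequal periods.

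Under the completion rule the imbalance is not random. Participants with simpler presentations are measured early and those with more complex ones late, while waitlist participants of every severity are measured at the same time. The regression in Section 15.3 uses a post-intervention period rather than elapsed weeks, so it does not settle the matter.

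**Working it through.** **The plan's own dates.** Section 12 counts follow-ups from endline, with up to one further month allowed. The check is endline window + k months, for k = 1, 3, 6.

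| Follow-up | Endline May 2025–Feb 2026, plus k | Latest, with tolerance | Stated window |
|---|---|---|---|
| 1 month | Jun 2025–Mar 2026 | Apr 2026 | Aug 2025–Jan 2026 |
| 3 months | Aug 2025–May 2026 | Jun 2026 | Oct 2025–Mar 2026 |
| 6 months | Nov 2025–Aug 2026 | Sep 2026 | Jan–Jun 2026 |

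None of the stated windows is reproduced. Each opens two months after the first visit falls due and closes two months before the last one does. The 1-month window closes in January 2026, a month before the last endline. Working backwards (stated window minus k), all three imply endlines from July to December 2025.

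**Elapsed time to endline.** Inputs:
- Sessions s = 6 to 12, weekly (Sections 2 and 8).
- Slipped weeks r = 0, or at most 6 if each of the six permitted reschedulings costs a full week. The full week is an assumption; the protocol does not say so.
- Time allowed after completion: 0 to 14 days, that is 0 to 2 weeks (Sections 2 and 12).
- L = weeks from baseline to session 1. The protocol does not state it.

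Completion in weeks after session 1 is c = (s − 1) + r. Counted from baseline, endline is L + c to L + c + 2 under the completion rule and L + 12 under the 12-week rule.

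| Course | c | Completion rule | 12-week rule | Waitlist |
|---|---|---|---|---|
| 6 sessions, r = 0 | 5 | L+5 to L+7 | L+12 | 12 |
| 12 sessions, r = 0 | 11 | L+11 to L+13 | L+12 | 12 |
| 12 sessions, r = 6 (assumed) | 17 | L+17 to L+19 | L+12 | 12 |

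For illustrative lags L = 0, 4 and 8 weeks, the completion rule spans weeks 5–19, 9–23 and 13–27 from baseline, and the 12-week rule gives weeks 12, 16 and 20. For a 6-session participant the two intervention-arm rules differ by 12 − 7 = 5 to 12 − 5 = 7 weeks.

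**Direction of the mean difference.** As an illustration, suppose sessions are spread evenly over 6 to 12, with no slippage and a visit mid-window. Mean sessions are 9, mean completion is week 8, and mean endline is week 9 after session 1. The mean mismatch is then L + 9 − 12 = L − 3 weeks: three weeks early at L = 0, none at L = 3, five weeks late at L = 8. The sign depends on a lag that the protocol does not give.

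**Data near week 12.** Questionnaires during treatment precede sessions and stop when sessions stop. A 6-session participant finishes at week 5 after session 1, and a follow-up one month after completion falls at about week 5 + 4.3 = 9.3. Under the completion rule, nothing is scheduled for week 12.

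**The case against.** The strongest defence is that the clocks may nearly agree in practice. Section 5 has treatment begin at randomisation in the intervention arm, enrolment is rolling, and the completion clause in Section 12 can be read as a mere tolerance around 12 weeks. With a short lag, both arms would then be measured at about 12 weeks. That reading is possible. It leaves first session and screening as different starting points, and it conflicts with Sections 2, 4.2.1 and 5.

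Several stronger inferences are tempting but not supported:

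- A reader might multiply a 5- to 7-week gap by an assumed natural improvement of 0.01 to 0.03 SD per week and report a bias of 0.05 to 0.2 SD. The protocol gives no such rate. The gap belongs to early finishers, whereas bias follows the mean difference, in which early and late visits partly cancel.
- A reader might treat weeks 17 to 19 as established. Section 8 offers flexible slots, so a session may move within its week.
- A reader might infer that the three start groups (February, May, August 2025) add a delay. They may simply follow recruitment.
- A reader might say the follow-up windows fit only a last endline in November 2025. That requires adding the tolerance month; without it the date is December 2025.
- A reader might say a 6-session participant reaches the 1-month follow-up before endline. That combines the completion anchor of Section 2 with the 12-week endline of Section 12; neither section produces it alone.

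The calendar rows are planning dates. Nothing says a visit outside them is dropped, and analysis runs to July 2027 in Section 12, so late visits could still be used. This part is secondary.

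Frequent questionnaires during treatment (PCL5 weekly, PHQ9 and GAD7 every two weeks) give data near week 12 for those still in sessions, but not for early finishers. How time is modelled may be left to an analysis plan. When participants are measured is fixed here, and modelling cannot replace a measurement that was not scheduled.

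**Conclusion.** The point stands as a contradiction in the protocol's assessment schedule that affects the primary comparison. The anchors differ between arms on the face of Section 12, and the intervention arm has two rules that disagree by 5 to 7 weeks for a 6-session course. Under the completion rule, timing also varies with symptom load. The week counts assume weekly sessions as stated; the upper limit of weeks 17 to 19 additionally assumes that each rescheduling costs a week.

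The effect on the estimated treatment difference may go either way, and its size cannot be given, because the baseline-to-session lag, the distribution of course lengths and the natural course of symptoms are all unstated. The conflicting follow-up anchors and calendar rows are real but smaller matters of scheduling.

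**What to change.** Define one endline for both arms: 12 weeks after randomisation, with the same window, regardless of sessions completed. State that this is the time point for the between-arm comparison. Counting from randomisation gives both arms the same scheduled interval, and any delay between screening and randomisation then falls on both arms alike. Keep the questionnaire after completion as a within-arm measure.

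State one anchor for the 1-, 3- and 6-month follow-ups in Sections 2, 4.2.1 and 12. Recompute the calendar rows from it, and reconcile the session rows, which spread 12 weekly sessions for the first group over February to August 2025, with the consecutive weeks stated in Sections 2 and 8.

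The cost is protocol wording and REDCap scheduling, plus one extra online form for participants whose completion falls away from week 12. Some intervention participants will be assessed before finishing. On the waitlist side, treatment follows endline (Section 2) and is placed 12 weeks after randomisation (Section 5). The window should therefore be applied so that it does not conflict with that stated start.

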There will be a planned variation in the dosage of the intervention, which can comprise 6 to 12 sessions. The exact number of sessions will be implemented according to the presentation of symptoms and difficulties of the participant. For instance, if the participant presents depressive symptoms concurrent with PTSD, then, strategies for the treatment of depression will be included alongside with strategies for the treatment of PTSD and the number of sessions will be higher. Also, some components identified as important for this population, such as problem solving or emotional regulation, could be added to the intervention, if they are identified as relevant for the specific participant. For instance, if - alongside with the CMD symptoms - the participant presents concrete problems that need to be tackled (e.g. precarious housing conditions, or lack of and need of childcare support), then the “problem-solving” component will be included as part of the intervention and the number of sessions will be higher. As described in detail in Section 8 “Study Intervention”, the first 6 sessions will be intended to treat the most urgent symptoms, and the following sessions will tackle other aspects relevant to the mental health of the participants.

As to the collection of data for the assessment of study objectives, the participant outcomes will be measured using validated instruments such as the PHQ9, GAD7, LEC5 and PCL5. In the case of the intervention group, all outcomes will be measured in the screening, after the last session and at 1-, 3- and 6-month follow-up. In the case of waitlist control, primary outcomes will be assessed at baseline during screening and at endline 12 weeks after baseline. For both the waitlist control and the intervention group, The PHQ9, GAD7, and PCL5 will be assessed throughout the intervention (which occurs at randomization for the intervention group, and 12 weeks after for the waitlist control group).

Furthermore, the assessment of secondary outcomes, such as acceptability and feasibility, will be measured as presented above, in section 4.

See the Appendix for a schematic of the study design.

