| Screening/baseline                                       | Begin: January 2025 and as potential participants contact research team until n =                                                                                    | Remotely via REDCap secure link (PHQ9, GAD7, PCL5, LEC5, demographics, exclusion criteria).                                                                                                                                                                                                                                                                                                                                                                                                                                                                                                                |
| Participation consent and enrollment                     | Begin: January 2025 and as potential participants contact research team until n = 90 is reached                                                                      | A link to the consent form will be sent via WhatsApp. A call will be scheduled to present the information on the study, clarify doubts and verify comprehension. Electronic consent will be collected via REDCap or DocuSign.                                                                                                                                                                                                                                                                                                                                                                              |
| Randomization and communication on begin of intervention |                                                                                                                                                                      | Remotely via telephone call
Demographics form via REDCap secure link
IPL via REDCap secure link                                                                                                                                                                                                                                                                                                                                                                                                                                                                                                      |

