| Session 1 (Orientation session)                          | 
First group of 30 participants:
February 2025
 
Second group of 30 participants:
May 2025
 
Third group of 30 participants:
August 2025
 | 
Individually with provider
Remotely via Meet or WhatsApp videocall
60 min duration
 
Focus on getting to know each other, goal-setting, session scheduling, rules for cancellation and re-scheduling.
                                                                                                                                                                                                                                                                                                                                                                                  |
| Sessions 2 to 6                                          | 
First group of 30 participants:
February 2025
-May 2025
 
Second group of 30 participants:
                                                       | 
Individually with provider
Remotely via Meet or WhatsApp videocall 60 min duration
 
Focus on symptom relief (depression, anxiety and/or PTSD)
                                                                                                                                                                                                                                                                                                                                                                                                                                             |

|                                     |                                                                                                                                                                                            |                                                                                                                                                                                                                   |

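### Endline is counted from first session or completion in the intervention arm but from baseline in the waitlist arm, so elapsed time is mixed with treatment

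*Protocol*

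**What the plan says.** The Endline row of the Section 12 table gives one rule per arm. For the intervention arm it reads "12 weeks after first session in intervention group (or within 14 days of completion"; for the waitlist arm, "12 weeks after baseline in waitlist control group".

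Elsewhere the intervention arm has a completion rule only. Section 2 (Subject Participation Duration) lists "1 online assessment of 30 min to be completed within 14 days after completion of the intervention". Section 5 says that in the intervention group "all outcomes will be measured in the screening, after the last session and at 1-, 3- and 6-month follow-up". Section 4.2.1 also places the assessment after the final session, and for the waitlist it states: "The primary outcomes will be measured at baseline during screening and at endline 12 weeks after baseline in the case of waitlist control". Section 2 (Design/Methodology) instead puts the waitlist's baseline at enrolment.

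On course length, Section 8 says: "It will comprise between 6 and 12 weekly sessions in consecutive weeks and will be delivered remotely via a video call". Sections 5 and 8 make the number of sessions depend on symptoms. Sections 8 and 9.1.2 allow up to six sessions to be rescheduled.

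Section 15.1 states a between-arm hypothesis. Section 15.3 describes trends over three labelled periods (baseline, post-treatment, six months later) and does not mention elapsed weeks.

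**The concern.** The protocol makes efficacy its primary objective (Section 4.1) and tests outcomes at two-sided 0.05 (Section 15.3). The contrast of interest is change in PHQ9, GAD7 and PCL5 between arms. People enter because at least one score is at or above a cut-off (10, 10 or 31 in Section 7.1), so some change is expected without treatment. Part of it, regression to the mean at the next measurement, is common to both randomised arms and largely cancels. The part that depends on how many weeks pass, such as natural recovery, does not cancel if the arms are measured after different numbers of weeks. Randomisation balances the people. It does not balance a follow-up length that the schedule sets by arm after allocation.

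Under the completion rule the interval also varies within the intervention arm with baseline severity, because dose follows symptoms.

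**Working it through.** The protocol states one interval, 12 weeks, for the waitlist. It gives no interval from baseline for the intervention arm, so that has to be derived.

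**Inputs**
- S = number of sessions, 6 to 12, weekly (Section 8). Session S falls S − 1 weeks after Session 1 if none is moved.
- Window after completion: 0 to 2 weeks (Sections 2 and 12).
- g = weeks from baseline to Session 1. Not stated in the text shown; 0, 2 and 4 are illustrations.
- r = weeks added by rescheduling. Up to six sessions may be moved; counting each as one extra week is an assumption.

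**Formulas, in weeks from baseline to endline**
- Waitlist: 12.
- Intervention, first-session rule: g + 12.
- Intervention, completion rule: g + r + (S − 1) to g + r + (S + 1).

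**Results with r = 0**

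| Intervention rule | g = 0 | Minus waitlist's 12 | g = 2 | g = 4 |
|---|---|---|---|---|
| Completion, 6 sessions | 5 to 7 | −7 to −5 | 7 to 9 | 9 to 11 |
| Completion, 8 sessions | 7 to 9 | −5 to −3 | 9 to 11 | 11 to 13 |
| Completion, 12 sessions | 11 to 13 | −1 to +1 | 13 to 15 | 15 to 17 |
| First session, any length | 12 | 0 | 14 | 16 |

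**Results with r = 6 and g = 0**
- Completion rule, 6 sessions: 11 to 13 weeks.
- Completion rule, 12 sessions: 17 to 19 weeks.
- First-session rule: still 12 weeks.

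**What follows**
1. The completion rule is not a tolerance around week 12 for short courses. At g = 0 and r = 0 its window for 6 sessions closes at week 7, five weeks before the first-session date.
2. The first-session rule matches the waitlist only when g = 0. Sections 10 to 12 place a follow-up call, a consent call and randomisation between screening and Session 1, so some gap is likely, but its length is not given.
3. The difference can go either way. Short courses under the completion rule give the intervention arm less time. A wait under either rule, or rescheduling of a long course under the completion rule, gives it more.
4. Follow-up inherits the ambiguity. Section 2 counts the 1-, 3- and 6-month visits from completion, and Section 12 counts them from endline. For a 6-session participant with g = 0, one month after completion at week 5 is about week 9, which is before a week-12 endline.

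**The case against.** **The calendar favours week 12 for short courses.** The Endline row is dated May 2025 to February 2026. A February starter with 6 sessions under the completion rule would be assessed between 8 March (1 February + 35 days) and 18 April (28 February + 35 + 14 days), before that row opens. Twelve weeks from a February start is 26 April to 23 May, which fits much better. On this reading the parenthesis serves late finishers. This stands to the extent that weeks 5 to 7 cannot be called the settled plan. It does not settle the matter, because Sections 2, 4.2.1 and 5 all describe a post-completion assessment. The calendar also looks indicative only: it spreads the first group's 12 weekly sessions from February to August.

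**A reader might infer long waits from the three start dates.** Enrolment is rolling ("Begin: January 2025 and as potential participants contact research team until n = 90 is reached"), while Session 1 is listed for 30 people at a time in February, May and August 2025. At most 30 of the 60 intervention participants can start in February, so at least 30 start later. That says nothing about when they were screened, since May starters may be screened in April. No enrolment pace is given, and the schedule of events is in an Appendix that is not shown. No average wait can be claimed.

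**A reader might also infer that these dates contradict Sections 5 and 10**, which have treatment begin at randomisation or immediately. They need not. The Randomization row carries no date, and randomising close to each wave satisfies both.

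**The design may suit a pilot.** The trial is sized to detect problems, compares trends, and has a variable dose for which a post-treatment time point is natural. That time point is worth keeping, but it has no counterpart in the waitlist arm.

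**Modelling actual time is ordinary analysis-plan content.** True, and it would help. Pre-session scores (PCL5 weekly, PHQ9 and GAD7 every two weeks) add information in the intervention arm. The waitlist has no score between baseline and week 12 and is treated afterwards, so its untreated course at week 6 or week 16 is never observed.

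**Conclusion.** The point holds as a defect in the schedule that the protocol itself fixes. No reading of the text shown gives the two arms the same anchor, and the two intervention rules disagree with each other. For a prompt 6-session course without rescheduling, the completion rule gives 5 to 7 weeks against the waitlist's 12. Under the first-session rule the intervention interval exceeds 12 weeks by exactly the gap between baseline and Session 1. Placing the waitlist baseline at enrolment, as one part of Section 2 does, would not align the arms either.

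The protocol does not show how large the resulting bias is, or which arm it favours. That depends on the mix of course lengths, the gap, the rescheduling and the rate of untreated change, and none of these is given. It would go too far to say that the trial's result will be biased in a known direction. The change should be made before the between-arm result is relied on, and it does not call the trial as a whole into question.

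**What to change.** - Set the between-arm endline for PHQ9, GAD7 and PCL5 at 12 weeks from randomisation in both arms, with the same visit window, and treat the waitlist only after it. Any time between screening and randomisation then precedes allocation and is common to both arms.
- Randomise close to the planned start, so that Session 1 follows within a short stated window. With Session 1 within one week and no rescheduling, the last of 12 sessions falls by week 1 + 11 = 12.
- Keep the 14-day post-treatment assessment as a separate within-arm time point, and say which of the two dates starts the follow-up clock.
- Use the same definition of baseline and endline in Sections 2, 4.2.1, 5 and 12.

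**Cost.** Protocol wording, and one extra remote REDCap assessment for participants whose course ends well before or after week 12. Some participants with rescheduled sessions will still be in treatment at week 12, which dilutes the effect seen there. A prompt 6-session completer will be about 12 − 5 = 7 weeks past the last session. In return, elapsed time is equal in both arms.
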